### Adverse event monitoring

#### Reporting of adverse events

At enrollment, participants are given contact information that they may use anytime (24 h a day/7 days per week) to report potential adverse events (AEs), which may include a physical, psychological, or laboratory event, or an increase in the severity or frequency of a pre-existing symptom or condition. Serious adverse events (SAEs) are defined by the International Conference on Harmonization of Technical Requirements for Registration of Pharmaceuticals for Human Use (ICH) as life-threatening, death, inpatient hospitalization/prolongation of existing hospitalization, congenital anomaly, persistent or significant disability/incapacity, and requirement of an intervention to prevent permanent impairment/damage [114, 115].

#### Documentation of adverse events

Participants are also informed at enrollment of their requirement to immediately report AEs/SAEs to the research team if and when they occur, and the research team will inquire about AEs/SAEs during telephone calls or home visits at weeks 6 and 12. Following AE/SAE reports, an AE form will be completed and reported to the clinic site physician and principal investigator. The contents of each form are reviewed for clarity by the principal investigator. Information regarding the time of event, severity, duration, and remedial actions (i.e., discontinuation of study supplement, physician follow-up, and treatment administered, if necessary) are documented on each AE form.

Participants who experience SAEs will be immediately withdrawn from the trial and these events will be reported to the principal investigator and clinic site physician within 24 h. The SAE will subsequently be reported to the U.S. Food and Drug Administration (FDA) Adverse Event Reporting System (AERS) and Natural MedWATCH, a tool developed and maintained by the Therapeutic Research Center’s Natural Medicines Comprehensive Database (https://naturaldatabase.therapeuticresearch.com/nd/adverseevent.aspx?s=ND&cs=naturalstandard) regardless of perceived causality to study intervention, followed by a report to the FDA including AEs not initially deemed reportable if the follow-up information causes a change in assessment. In accordance with Good Clinical Practice (GCP) guidelines [116], the informed consent form (ICF) will also be revised when new information becomes available that may be relevant to the participant’s consent, including the addition of new AEs related to the study treatment.

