### Intervention

#### Arrangement for intervention

This study is a multi-site clinical trial, with treatment allocation randomized a priori within each site. This study has received Institutional Review Board (IRB) approval. All research staff have experience with clinical trial recruitment, consenting procedures, and management of clinical and community interventions, and have been trained to uniformly implement all procedures relevant to this study prior to participation. After providing informed consent, participants are instructed on the details of their involvement in the study, including how to use their daily dietary supplement (or placebo) and study diary. Each participant has an in-person baseline assessment, a telephone assessment at 6 weeks, and an in-person assessment at 12 weeks.

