All participants visit their clinic site for two total visits over the 12-week study (i.e., baseline and at 12 weeks). Each visit includes blood sampling. Participants receive their study supplement from the same outpatient physician office, health clinic, or at a home visit. Participants are instructed on how to take the supplement and given appropriate contact information to use for questions or to alert study personnel of any potential adverse events. Each participant receives a bottle labeled only with a group-level identification number unique to randomization group (for which the master study code is accessible only through a locked cabinet by a study coordinator), directions for use, primary research site name, batch number, and IRB protocol number. Participants are asked to record any changes in symptoms and medication or nutritional supplement use in a daily diary using a form reviewed at each study time point.

The intervention and placebo capsules are from the same lot. The placebo utilized in this clinical trial is an inactive dietary supplement composed of cellulose, microcrystalline cellulose, silicon dioxide, and vegetable stearate, and formulated by the manufacturer to be as similar as possible to the active intervention in appearance and other key characteristics. In an attempt to match scent, both active intervention and placebo will have their lid undersides swabbed with a cotton ball containing one drop of cinnamon essential oil (steam-distilled *Cinnamomum zeylanicum* leaf). Packaging for the control group is identical to packaging for the treatment group.

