This study will utilize an adaptive sample size re-estimation (SSR) approach [107] where participant enrollment may be extended beyond the originally planned sample size if interim effect size is smaller than anticipated, but still promising, thereby preserving study power. The adaptive SSR technique will include: (1) examination of available unblinded endpoint data by the study statistician after 30 subjects are enrolled, (2) calculation of conditional power (CP), and (3) sample size modification in order to maintain study power, if required, based on pre-defined limits. CP is defined as the power of rejecting the null hypothesis at the end of the trial conditional on the observed data accumulated up to the time of the planned interim analysis. CP estimates will be categorized into one of three “zones”— Favorable, Promising, or Unfavorable. The Favorable zone will be defined as CP ≥ 80%. CPs in the Favorable zone will require no sample size adjustment (*n* = 40). Similarly, CP estimates that fall into the Unfavorable zone (CP < 50%) will require no sample size modifications (*n* = 40). However, if CP falls into the Promising zone (CP between 50 and 79%), the sample size will be recalculated such that CP equals the originally planned statistical power (i.e., 80%), up to a maximum of 66 subjects. This methodology preserves the overall type I error rate, no adjustments to alpha levels or confidence intervals are necessary, and standard statistical tests can be used for data analysis. Should the trial need to utilize adaptive SSR and enroll to the maximum sample size of 66, a difference in group means of 0.74 standard deviations could be detected.

Participants will be withdrawn from the study if they wish to withdraw or experience serious adverse events (SAEs) for any reason. If SAEs are reported, the site physician and principal investigator of the study will be contacted by the study coordinator, the participant will be withdrawn from the study, and a treatment plan will be implemented. Any dropouts will be included in the statistical analysis as intention-to-treat (ITT) using the last value carried forward (LOCF) method. Subsequent analyses will also be conducted on the per-protocol population which fully completes the study in order to determine if there are any discernible differences in these populations for the purposes of more broadly extrapolating the generalizability of results.

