#### Safety indices

Alanine aminotransferase (ALT) levels to assess hepatic functionAspartate aminotransferase (AST) levels to assess hepatic function

Both safety indices will be tested on visit 1 (baseline visit) and visit 2 (at 12 weeks).

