#### Analysis of datasets

Full analysis of ITT: the LOCF method will be used for missing data pointsPer-protocol set (PPS): PPS analyses will include participants who meet the following characteristics: meet inclusion criteria, are between 75 and 107% compliant with dosing per self report [121], have complete laboratory assessments, have primary outcome measurements within the study timelineSafety set (SS): the incidence of reported AEs/SAEs will be identified for all documented safety outcomes; biomarkers will be assessed according to laboratory test results

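### A serious adverse event ends trial participation, not just supplement use, so an avoidable missing week-12 outcome enters the primary ITT analysis as zero change

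*Protocol article*

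**What the plan says.** The withdrawal rule appears twice in the protocol article. Under Documentation of adverse events: "Participants who experience SAEs will be immediately withdrawn from the trial". Under Sample size: "Participants will be withdrawn from the study if they wish to withdraw or experience serious adverse events (SAEs) for any reason". Both refer to the trial or study as a whole, and the second sets aside causality.

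On missing data, Sample size states: "Any dropouts will be included in the statistical analysis as intention-to-treat (ITT) using the last value carried forward (LOCF) method". Analysis of datasets repeats LOCF for the ITT set, and Statistical analysis methods makes ITT the primary analysis.

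On the schedule, Arrangement for intervention states: "Each participant has an in-person baseline assessment, a telephone assessment at 6 weeks, and an in-person assessment at 12 weeks". Polyherbal dietary supplement intervention adds "All participants visit their clinic site for two total visits over the 12-week study (i.e., baseline and at 12 weeks" and "Each visit includes blood sampling". For ALT and AST, Safety indices states: "Both safety indices will be tested on visit 1 (baseline visit) and visit 2 (at 12 weeks". Data collection points lists no follow-up period.

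Criteria for the evaluation of safety ties the judgement that the supplement is relatively safe to little or no change in ALT and AST, and adds a list of symptoms captured through adverse event reports. The same section lets the study physicians decide whether to suspend the supplement, and provides for follow-up of participants with SAEs and an attempt to establish the cause.

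**The concern.** Stopping a treatment and leaving a trial are different events. An ITT analysis should use the outcomes of randomised participants wherever they can be obtained, including after treatment has stopped. This rule ends participation automatically, so the protocol itself creates missing outcomes in people who may be willing and able to give a week-12 sample. It then fills the gap with an assumed zero change.

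The rule also removes the scheduled liver enzyme measurement from participants who have just had a serious event, in a trial where those enzymes are a stated safety criterion. An unrelated hospital admission is enough to trigger it.

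**Working it through.** **Tracing the rules.**

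1. An SAE before the week-12 draw leads to immediate withdrawal from the trial.
2. The only earlier blood draw is at baseline, since week 6 is a telephone contact.
3. LOCF sets the week-12 value equal to baseline, so change = baseline − baseline = 0 for every glycemic, lipid and inflammatory outcome.
4. The ITT set with these values is the primary analysis set. The mixed model does not undo this if the data are first filled by LOCF.
5. The per-protocol set requires participants to "have complete laboratory assessments, have primary outcome measurements within the study" timeline, so it holds no observed week-12 value for this person either.
6. ALT and AST are due only at the two visits, so no further liver test is scheduled.

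An SAE at or after the week-12 draw is not affected.

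**Reproducing the plan's figure.** Inputs from Sample size: difference 0.91 SD, two-sided alpha 0.05, equal-variance t test, 20 per arm. Power comes from the noncentral t distribution with 2n − 2 degrees of freedom and noncentrality δ√(n/2).

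- n = 20: noncentrality 0.91 × √10 = 2.88, power 80.1%. This matches the planned 80%.
- n = 22 (all 44 enrolled are analysed): noncentrality 0.91 × √11 = 3.02, power 83.9%.

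**Size of one case.** Assumptions, not in the document: 22 analysed per arm, no mean change on placebo, and one active-arm participant set to zero change.

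- Share of the arm: 1/22 = 4.5%.
- Expected difference: 0.91 × 21/22 = 0.869 SD.
- Power at 0.869 SD with 22 per arm: 80.4%. A simulation with one value fixed at zero gave 80.9%.
- Two such cases: 0.91 × 20/22 = 0.827 SD, power 76.4%.

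**LOCF against the real week-12 value.** Let r be the fraction of the 0.91 SD effect that this participant would show at week 12. With the value observed, the expected difference is 0.91 × (21 + r)/22.

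| r | Expected difference, value observed (SD) | LOCF (0.869) minus observed (SD) |
|---|---|---|
| 1 (full effect persists) | 0.910 | −0.041 |
| 0.5 | 0.889 | −0.021 |
| 0 (effect lost) | 0.869 | 0 |
| −0.5 (worsens by 0.455 SD) | 0.848 | +0.021 |
| −1 (worsens by 0.91 SD) | 0.827 | +0.041 |

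LOCF understates the difference if some benefit persists. It overstates the difference if the participant deteriorated.

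**The case against.** The strongest reply is that nothing the trial can conclude is likely to change. No SAE rate is given, the trial is described as proof-of-concept and exploratory, and one active-arm case leaves power at 80.4%, still at the planned level. The drop is visible only against 83.9%, which the plan never claims. That stands, and it is why the point is minor.

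A second reply is that LOCF with two draws is the real source of error. It affects every early dropout, and the plan allows for 10% attrition. This is partly right, and correcting the SAE rule leaves those other dropouts untouched. But other dropouts may be lost for reasons the protocol cannot control, whereas here the protocol orders the loss.

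A third reply concerns safety. SAEs are recorded, reported and counted, symptoms are assessed through adverse event reports, relatedness is judged partly on whether the event resolved after stopping, and physicians follow up. All of this is true, so clinical safety follow-up is not absent. None of it schedules a week-12 outcome or an ALT/AST test.

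Finally, a fuller protocol might contain an early-termination draw. The article is condensed, so this cannot be excluded. But the concern rests on an explicit rule of immediate withdrawal combined with a stated schedule and imputation method, and an analysis plan cannot recover blood that was never drawn.

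**Conclusion.** The concern holds, as a modest improvement and not a threat to the trial. As written, any SAE before the week-12 draw produces a missing outcome that may have been avoidable, and the primary analysis treats it as zero change.

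Under the assumptions shown, each active-arm case carries 4.5% of the arm's weight and shifts the estimate by up to about 0.04 SD in either direction relative to the true week-12 value, across the range of outcomes considered. The number of cases is unknown and may be zero. On the safety side, the loss is one scheduled ALT/AST measurement for each affected participant.

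**What to change.** Amend Sample size and Documentation of adverse events so that an SAE leads to stopping the supplement at the study physicians' discretion, which Criteria for the evaluation of safety already gives them, without ending participation. Unless consent is withdrawn or attendance is impossible, keep the planned adverse event contacts and the week-12 blood draw, including ALT and AST. Use the observed values in the ITT and safety analyses, and restrict LOCF to participants with no week-12 value.

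The cost is a short amendment with IRB approval and perhaps a few off-supplement visits. The visit, the bloods and the contacts are already planned, and the sample size does not change. There are two limits: an ALT/AST taken weeks after stopping may say little about liver effects on treatment, and after some SAEs no visit will be possible.

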#### Relationship between adverse events and study treatments

Researchers will determine the potential causality between the study supplement and reported AEs/SAEs using the following criteria to determine severity and relatedness:Whether the suspected AE/SAE appears after treatment administration, in addition to history of symptom(s) associated with the suspected AE/SAEWhether the suspected AE/SAE belongs to known or suspected potential adverse reactions of the study supplement; these include: dizziness, skin rash, headache, tinnitus, hyper/hypotension, and gastrointestinal eventsWhether the AE/SAE dissipated or disappeared after discontinuation of the study supplementWhether a participant’s health history or co-occurring medicine or supplement use may be responsible for the AE/SAE (to be determined by the principal investigator and/or study physicians)

#### Criteria for the evaluation of safety

The safety of the study supplement will be assessed as relatively safe without any, or minimal, changes in hepatic function (ALT, AST).

In addition, nausea, vomiting, loss of appetite, fatigue and weakness, sleep problems, changes in urination, decreased mental sharpness, muscle twitches and cramps, swelling of feet and ankles, persistent itching, chest pain, shortness of breath, and uncontrollable high blood pressure [117–120] will be assessed via the reporting of all AEs/SAEs. The study physicians will determine potential suspension of study supplement, if necessary, and will follow-up with all participants reporting SAEs and attempt to perform medical evaluation to determine the cause of the SAE and its possible relationship to the study intervention.

### Statistical analysis plan

#### Analysis software

All parameters will be analyzed using SAS v9.4 (Cary, NC, USA).

#### Analysis of datasets

Full analysis of ITT: the LOCF method will be used for missing data pointsPer-protocol set (PPS): PPS analyses will include participants who meet the following characteristics: meet inclusion criteria, are between 75 and 107% compliant with dosing per self report [121], have complete laboratory assessments, have primary outcome measurements within the study timelineSafety set (SS): the incidence of reported AEs/SAEs will be identified for all documented safety outcomes; biomarkers will be assessed according to laboratory test results

### Statistical analysis methods

The number of participants screened, randomized, withdrawn early, and completing the study will be tabulated by treatment group and presented in a Consolidated Standards of Reporting Trials (CONSORT)-herbal diagram [122]. Reasons for early withdrawal, if any should occur, will be presented.

Descriptive statistics will be computed for baseline and demographic characteristics and tabulated by treatment group, and may include means, medians, standard deviations, inter-quartile ranges, and percentages, as dictated by the form of each variable. Independent *t* tests will be used for group comparisons (polyherbal dietary supplement group versus control group) on primary and secondary outcomes for each time point. Data transformations may be performed in the event of non-normally distributed data, or the Wilcoxon-Mann-Whitney non-parametric test will be used to assess differences between the means of outcomes between both groups. Fisher’s exact chi-square will be used to assess differences in categorical variables by group, in order to establish whether additional possible influences of dietary intake, broad differences in physical activity, or other demographic differences between study groups may accompany changes in any of the outcomes of interest. The chi-square test will be used for comparing additional endpoint events (e.g., incidence of T2D).

Study outcomes over the 12-week supplementation period will be analyzed using a mixed-model analysis of variance for continuous variables, which controls for within-subject and between-subject correlation. Repeated measures analysis of variance and logistic regression will be used to evaluate potential changes in physical activity and dietary intake, in order to determine whether these differ by treatment group to potentially influence observed effects of the intervention. If applicable, the proportion of subjects reporting at least one AE will be tabulated in each treatment group and compared using Fisher’s exact test. Statistical significance will be set at *p* < 0.05. No adjustments for multiplicity will be performed. The primary analysis will be conducted on the ITT population. Per-protocol and sensitivity analysis may be conducted as appropriate.

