### Randomization and blinding

Treatment assignment is randomly assigned, in a 1:1 ratio, at each site using a block size of 6. The block randomization sequence schedule is password-controlled by an appointed research team member not involved in the screening or enrolling of participants. The treatment assignments are known to the study coordinator who maintains the allocation master list in a sealed, opaque envelope. Participants, treating clinicians, and outcome assessors are blinded to intervention group status.

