### Sample size

The research team aims for a final sample of 40 participants with prediabetes in this clinical trial. Participants are recruited from within clinical practices, mobile health screenings conducted as part of a separate non-intervention study [106], support groups, and health fairs, with 20 participants allocated to the active group (GlucoSupreme™ Herbal) and 20 participants allocated to the control group (placebo). In order to account for a conservative and higher-than-expected dropout rate of 10%, 44 participants will be enrolled to achieve the target sample size. The sample size of 44 participants was estimated by assuming 80% statistical power, a significance level (alpha) of 0.05 using a two-sided, two-sample, equal variance *t* test, an anticipated difference in group means of 0.91 standard deviations for continuous variables, and 10% attrition. The sizes of these treatment effects are large (i.e., between-group differences will need to be considerable in order for the treatment to demonstrate statistically significant improvements relative to placebo).

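### The protocol sets two different tests for the same primary outcomes without saying which decides; one baseline- and site-adjusted ANCOVA would settle this and use data already collected

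*Protocol article*

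**What the plan says.** Under Statistical analysis methods, the protocol article sets independent *t* "tests will be used for group comparisons (polyherbal dietary supplement group versus control group) on primary and secondary outcomes for each time point". Transformation or the Wilcoxon-Mann-Whitney test is available if the data are not normal. The next paragraph states: "Study outcomes over the 12-week supplementation period will be analyzed using a mixed-model analysis of variance for continuous variables". The word primary is attached there to the ITT population and not to either method.

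Under Sample size, the trial is sized on the unadjusted test: "a significance level (alpha) of 0.05 using a two-sided, two-sample, equal variance" *t* test, with "an anticipated difference in group means of 0.91 standard deviations for continuous variables, and 10% attrition", for 20 participants per arm.

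Blood is sampled at two visits only, baseline and week 12; week 6 is a telephone contact. Randomization and blinding states that assignment is made 1:1 "at each site using a block size of 6". Neither analysis statement names site.

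The Sample size section also has an interim step: conditional power is calculated on unblinded data after 30 participants are enrolled, and it decides whether enrolment is extended, up to 66.

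**The concern.** The *t* test at week 12 and the mixed model's group-by-time contrast are different statistics on the same outcome. They can give different answers, and the protocol gives no order between them. Two things follow.

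- **Error rate and interim rule.** If either test may carry the claim, the 5% level is not kept. Conditional power is defined for one null hypothesis and one final test. Two candidate tests can give two values, and so different sample-size zones.
- **Precision.** The *t* test uses neither the baseline value, which every participant will have, nor the site within which allocation was blocked. With 20 per arm and a large target effect, precision that is already paid for should be used.

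A smaller matter: because laboratory values exist only at baseline and week 12, one of the *t* tests at each time point compares randomised groups before treatment. Any difference found there is chance.

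**Working it through.** **Inputs from the protocol:** two-sided alpha 0.05; 80% power; difference 0.91 SD; 20 per arm; two laboratory time points; 1:1 allocation blocked within site.

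**Assumed, because the protocol gives no figure:** baseline-to-week-12 correlation r of 0.3 to 0.8; equal SD at both visits; three sites; site share of outcome variance 5% to 30%.

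**1. The plan's own figures.** For the *t* test, the noncentrality is 0.91 × sqrt(20/2) = 2.88 on 38 df, which gives power of 80.1%. The stated size reproduces. Attrition: 40 × 1.1 = 44 (40/0.9 rounds up to 45, a trivial difference). The 0.74 SD quoted for the maximum of 66 reproduces with about 60 completers (0.736 SD).

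**2. Variance of the treatment difference, relative to the week-12 *t* test**

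- week-12 *t* test: 1
- change score (group-by-time with two visits): 2(1 − r)
- ANCOVA on baseline: 1 − r²

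Since 2(1 − r) − (1 − r²) = (1 − r)², the change score is never more precise than ANCOVA. It beats the *t* test only if 2(1 − r) < 1, that is, r > 0.5.

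**3. Power at 20 per arm and 0.91 SD.** The standardised effect is 0.91/sqrt(variance factor). ANCOVA has 35 df (38, less one for baseline and two for three sites). MDD is the difference detectable with 80% power, in SD.

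| r | *t* test power | Change-score power | ANCOVA power | *t* test MDD | Change-score MDD | ANCOVA MDD |
|---|---|---|---|---|---|---|
| 0 | 80.1% | 50.9% | 79.9% | 0.91 | 1.29 | 0.91 |
| 0.3 | 80.1% | 65.9% | 83.5% | 0.91 | 1.08 | 0.87 |
| 0.5 | 80.1% | 80.1% | 89.8% | 0.91 | 0.91 | 0.79 |
| 0.7 | 80.1% | 95.2% | 97.5% | 0.91 | 0.70 | 0.65 |
| 0.8 | 80.1% | 99.3% | 99.7% | 0.91 | 0.58 | 0.55 |

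These ANCOVA figures leave out the small cost of estimating the baseline slope. Taking about 19.5 effective participants per arm instead gives 89.2% at r = 0.5 and 97.2% at r = 0.7.

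**4. Site alone** (simulation with three sites, 40,000 runs; adjusted power by formula)

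| Site share of variance | True alpha, *t* test | Power, *t* test | Power with site in the model |
|---|---|---|---|
| 5% | 0.044 | 80.6% | 81.9% |
| 10% | 0.039 | 81.3% | 83.9% |
| 20% | 0.029 | 82.3% | 87.9% |
| 30% | 0.019 | 83.7% | 91.7% |

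**5. Two tests, one outcome** (simulation under the null, 20 per arm, 100,000 runs for each r). Each test alone holds 5%.

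| r | Either test p < 0.05 | Tests disagree |
|---|---|---|
| 0.3 | 8.9% | 7.7% |
| 0.5 | 9.0% | 8.1% |
| 0.7 | 9.4% | 8.7% |
| 0.8 | 9.5% | 9.0% |

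**The case against.** The sizing test and one of the stated tests agree, and the stated power is right. An unadjusted *t* test in a randomised trial is valid, so on this view the preference for ANCOVA is only a preference. The gain rests on a correlation that the protocol does not give: about 3.5 points at 0.3 and nil at 0. Covariates in the mixed model, including site, may be in an analysis plan that is not shown.

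Most of this stands, and it rules out several stronger readings that a reader might draw:

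- **That the primary comparison ignores baseline.** The protocol never calls the *t* test primary, and the mixed model takes baseline in as a repeated measure. The statement is true of the *t* test only.
- **That chance baseline imbalance biases the result.** At 20 per arm the baseline difference has SD sqrt(2/20) = 0.32. It enters the week-12 difference multiplied by r (0.16 SD at r = 0.5, 0.22 SD at r = 0.7), and the *t* test's variance already allows for it.
- **That leaving out site inflates error.** It makes the *t* test conservative.
- **That the trial is undersized.** It is not, for the test it was sized on.
- **That an unblinded statistician will pick the test.** The protocol has the study statistician see unblinded data for conditional power, but does not say who chooses the deciding test.

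What the objection does not remove is that the article itself fixes two analyses for the same outcomes and ranks neither. An unseen plan could rank them, but the published text does not.

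**Conclusion.** The point holds as a specification fault with an inexpensive improvement attached, and not as an error in validity or sample size. Two analyses compete for the same continuous primary outcomes. The figure of about 9% type I error per outcome applies only if either test may carry the claim. The protocol does not state that rule, but does not exclude it. It concerns a single outcome and is separate from the number of primary outcomes.

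The ANCOVA gain is roughly 3 to 20 percentage points of power for correlations of 0.3 to 0.8, and zero at 0. At r = 0.7 the detectable difference is 0.65 SD with 20 per arm, smaller than the 0.74 SD that the protocol reaches by enrolling up to 66. The change-score test is the weakest of the three below r = 0.5 and is below ANCOVA throughout. Any benefit from site comes on top and depends on how much the sites differ. The correlation, the site share of variance and the number of sites are all assumptions.

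**What to change.** Under Statistical analysis methods, name one primary analysis for each continuous primary outcome: ANCOVA of the week-12 value, or the equivalent baseline-constrained mixed model, with treatment, baseline value and site. Use that same model for conditional power and for any recalculated sample size. Label the unadjusted *t* test, the Wilcoxon-Mann-Whitney test and the change-type mixed model as sensitivity analyses. Drop the between-group significance test at baseline and describe baseline values only. The planned sample size can stay as it is.

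The cost is a protocol amendment, which the protocol says needs IRB approval, and about three degrees of freedom if there are three sites. No new data are needed. The trial was recruiting at submission, so the change should be dated and made before the interim look. If that look has already taken place, it should be made by people who have not seen unblinded results.
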